**Figure 1 Fig1:**
[figure not shown]
**FEMME trial eligibility flow chart.** UAE, uterine artery embolization.

### Patient information

Women will be identified primarily by gynaecologists in dysmenorrhea or general gynaecology clinics, but a small minority may be referred directly to an interventional radiologist. In the latter case, potential participants will need to be reviewed by a gynaecologist to ensure they are suitable for myomectomy.

Depending on local practice and staff availability, the referral letters may be screened by the research nurse who will bring to the gynaecologist’s attention those women whose symptoms are suggestive of uterine fibroids and who may be eligible to take part in the FEMME trial. After review, should the gynaecologist agree that uterine fibroids are the likely underlying cause of the described symptoms, they can request the nurse sends out a Research Ethics Committee (REC)-approved participant information sheet (PIS) and covering letter in advance. This will allow the woman to be aware of the FEMME trial before she attends the clinic for her appointment. This stage is optional and dependent on local practice and gynaecology agreement.

When the woman presents in clinic she will be reviewed by a qualified gynaecologist. Following confirmation of the presence of fibroids, if the gynaecologist feels that these will respond equally well to UAE or myomectomy, then the gynaecologist will make the initial approach to the women to make them aware of the FEMME trial. If the woman expresses an interest in taking part in the FEMME trial then an approved member of the local research team will discuss the protocol with them and answer any queries they may have.

### Consent

Consent will be obtained from any potential participant in compliance with the requirements of the REC before they are included in the trial. Any potential participant will only be approached by an approved member of the local research team. The potential participant will be given a copy of the REC-approved PIS, setting out the nature and purpose of the study, alongside the possible risks and benefits of taking part. The approved member of the local research team will fully discuss the trial with the potential participant and answer any questions they may have prior to consent being taken. Any potential participant will be informed that they can withdraw from the trial at any point without having a give a reason why. Should they wish to withdraw, then the patient will be reassured that the medical care they receive will not be affected in any way. The patient’s consent will be recorded on a REC-approved consent form and countersigned by the approved member of the local research team. Once signed and dated by all parties, the participant will be given a copy of the consent form for their own records.

### Randomisation

In order to reduce bias as far as possible, following informed consent but before randomisation, the participant will be given the validated QoL questionnaires (the UFS-QoL and the EuroQoL EQ-5D) and asked to complete them. Once completed and returned to the clinical staff, the patient’s details will be entered onto a centralised online system which will allocate the patient to their treatment (myomectomy or UAE). A minimisation algorithm will be used to ensure that the groups are balanced as evenly as possible with respect to treatment group and also the following variables: the longest dimension of the largest fibroid (under 7 cm or over 7 cm), the number of fibroids present (1 to 3, 4 to 10, over 10), and if the woman desires pregnancy (yes or no).

The number and size of the fibroids present will be determined by imaging with either: magnetic resonance imaging (MRI) (contrast enhanced and/or non-contrast enhanced), ultrasound (vaginal or trans-abdominal), or hysteroscopy.

Should a participant have been randomised on any type of imaging other than MRI then, if local capacity allows, an MRI scan will be requested prior to the patient undergoing their procedure. After randomization, blood will be drawn into two BD Vacutainer® serum separator tubes (SST, BD, [name]) for the proxy measurement of ovarian reserve. These blood samples will be placed into a Royal Mail Safebox™ and sent to Birmingham University’s Human Tissue Repository. Upon receipt, the blood samples will be transformed into serum and stored in a secure biobanking facility at −80°C until analysis. Finally, the participant will be given a copy of the menstrual blood loss diary to take away with them and asked to complete it when they start their next period. Upon completion this blood loss diary will be returned to the trials office in a prepaid envelope provided.

### Treatment

A pregnancy test will be performed immediately prior to treatment. As FEMME is a pragmatic trial, other than the randomisation to myomectomy or UAE the treatment the woman receives is the clinician’s normal practice. This means that if the woman is randomised to a myomectomy this can be of any type including laparoscopic, hysteroscopic, or by a laparotomy. Similarly, should the woman be randomised to UAE, this is performed according to the interventional radiologist’s normal practice. Information collected at the time of the procedure will include details of the treatment received, any adverse events experienced by the participant, and the length of in-patient stay.

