With increasing pressure on ever diminishing NHS budgets the cost-effectiveness is increasing in importance to commissioners and Trusts when deciding which treatment options should be available. The average length of stay in hospital post-hysterectomy is 4.4 days [10], and it is not unusual for women to require an additional three months to recuperate before returning to their normal lives. The average stay in hospital post-myomectomy is 3.6 days and, depending on the route used, the post-procedure recuperation time can be up to several weeks. With its minimally invasive nature, the mean length of hospital stay post-UAE is one day, with a return to normal life typically within a couple of weeks. Whilst superficially this may suggest a significant economic advantage for UAE, the higher re-intervention rates compared with hysterectomy may well negate any cost saving by five years [10].

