### Secondary outcomes

The FEMME trial’s secondary outcomes are:EuroQoL EQ-5D score and visual analogue scale score;Menstrual blood loss, assessed using the Pictorial Blood loss Assessment Chart (PBAC). This is a validated and well-used assessment of menstrual blood loss in women with uterine fibroids;Pregnancy outcomes - pregnancy will be reported by the woman in the first instance. The research nurse or trial coordinator will collect further information with respect to timing of pregnancy, biochemical pregnancy (positive pregnancy test), incidence of miscarriage, outcome of pregnancy, gestational age at delivery or miscarriage, complications of pregnancy, and labour;Adverse events - all adverse outcomes considered to be related to the study protocol or intervention will be collected. Since adverse outcomes may occur many months after intervention, these data will continue to be collected throughout the study;Length of hospital stay;Time to return to work or usual activity;Further treatment for incomplete removal or recurrence of symptoms, including hysterectomies;Ovarian reserve - blood samples will be taken from the women in each treatment arm for the measurement of the plasma levels of Anti-Müllerian hormone (AMH), a compound used as a proxy measurement of ovarian reserve, to determine if there is any difference at six weeks, six months, and twelve months post-procedure.

The time-points at which these follow-ups are performed are shown in Table 1.

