**Table 1 Tab1:** **Time-points at which outcomes are recorded**

Outcome measure	Prior to randomisation	Before discharge	6 weeks	6 months	1 year	2 years	4 years
UFS-QoL/EQ-5D	×			×	×	×	×
Pregnancy				×	×	×	×
Outcomes of pregnancy					As reported by participant		
PBAC	×			×	×	×	×
Fertility potential	×		×	×	×		
Resource usage (clinical)	×	×		×			
Technical success				×			
Serious adverse events					As reported by clinician/participant		
Further treatment				×	×	×	×

Legend:

UFS-QoL: Uterine Fibroid Symptoms – Quality of Life.

EQ-5D: EuroQol – 5D score and visual analogue scale score.

PBAC - the Pictorial Blood loss Assessment Chart.

With an increasing number of women seeking an alternative to hysterectomy, this timely trial will investigate the role of UAE and myomectomy in treating women with symptomatic uterine fibroids, and so inform women as to the most appropriate treatment for them.

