#### Monitoring of all types of adverse event

All types of adverse event which occur to participants in the FEMME trial will be reported as soon as possible after the clinician becomes aware of the event. An adverse events form should be completed as fully as possible and sent via fax to the trials office. This form will include an assessment of causality. Upon receipt, the trials office will log details of the adverse event on that patient’s record on the central trials database and forward an anonymised copy of the form to the sponsor and the Chief Investigator. Anonymised details of all adverse events will be presented to the DMC for scrutiny each time they meet. These anonymised details will be reported to the REC annually.

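### After the procedure, adverse events are captured only if someone reports them, so the early safety comparison in this open trial rests on unequal intensity of observation

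*Protocol article*

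**What the plan says.** The protocol article deals with adverse events in four places.

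- **Treatment:** they are part of the procedure record. "Information collected at the time of the procedure will include details of the treatment received, any adverse events experienced by the participant". Length of in-patient stay is a further item in the same list.
- **Secondary outcomes:** adverse events are a named secondary outcome, with the scope "all adverse outcomes considered to be related to the study protocol or intervention will be collected" and the period "Since adverse outcomes may occur many months after intervention, these data will continue to be collected throughout the study".
- **Table 1:** the row for serious adverse events has no marked time-point, only "As reported by clinician/participant". There is no row for non-serious events. The 6-week column is marked only for fertility potential.
- **Monitoring of all types of adverse event:** events "will be reported as soon as possible after the clinician becomes aware of the event". The reports go to the Data Monitoring Committee at each meeting.

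Two other places matter. The Follow-up section asks both arms about additional visits and their reasons, procedures, inpatient stays, medications and tests, but as resource use. The Background gives typical stays: "The average stay in hospital post-myomectomy is 3.6 days", and "the mean length of hospital stay post-UAE is one day".

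**The concern.** The plan fixes how long adverse events are collected but, after the procedure record, not that anyone asks about them. Later capture depends on the woman or a clinician volunteering a report.

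That matters here for two reasons. First, the trial is open, so awareness of the treatment can influence what is reported. Second, the arms are expected to differ in time spent on a ward. An event on the second or third day may be seen by staff after myomectomy, yet depend on a report from home after UAE. The protocol itself notes that "adverse outcomes may occur many months after intervention", so the gap is not confined to the first days.

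At stake is the between-arm comparison of a named secondary outcome, and the picture that the Data Monitoring Committee sees while the trial runs. Complications are one of the main trade-offs between the two procedures.

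**Working it through.** **Step 1: period against method.** The article gives no figure for adverse-event capture, so there is nothing of the plan's own to reproduce. Set side by side, the sections read:

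| Place | Period | How events come to light |
|---|---|---|
| Treatment | at the procedure | recorded as a data item |
| Secondary outcomes | whole study, both arms | not stated |
| Table 1 (serious events only) | no time-point marked | report by clinician or participant |
| Monitoring section | no limit | clinician becomes aware |
| Follow-up | each time-point | asked, but as resource use |

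The period is equal between arms. The only set moment for adverse events as such is the procedure record.

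**Step 2: how much could this matter?** From the document: stays of 1 day (UAE) and 3.6 days (myomectomy), which are background means. Assumed: equal true risk in both arms, events spread evenly over *T* days, full capture while in hospital, and a fraction *r* captured after discharge, the same in both arms.

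Capture = [stay + (*T* − stay) × *r*] / *T*, and the spurious risk ratio is UAE capture divided by myomectomy capture.

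*T* = 14 days:

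| *r* | UAE | Myomectomy | Ratio |
|---|---|---|---|
| 0.3 | (1 + 13 × 0.3)/14 = 0.350 | (3.6 + 10.4 × 0.3)/14 = 0.480 | 0.73 |
| 0.5 | (1 + 13 × 0.5)/14 = 0.536 | (3.6 + 10.4 × 0.5)/14 = 0.629 | 0.85 |
| 0.8 | (1 + 13 × 0.8)/14 = 0.814 | (3.6 + 10.4 × 0.8)/14 = 0.851 | 0.96 |

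*T* = 42 days:

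| *r* | UAE | Myomectomy | Ratio |
|---|---|---|---|
| 0.3 | (1 + 41 × 0.3)/42 = 0.317 | (3.6 + 38.4 × 0.3)/42 = 0.360 | 0.88 |
| 0.5 | (1 + 41 × 0.5)/42 = 0.512 | (3.6 + 38.4 × 0.5)/42 = 0.543 | 0.94 |
| 0.8 | (1 + 41 × 0.8)/42 = 0.805 | (3.6 + 38.4 × 0.8)/42 = 0.817 | 0.98 |

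Over 730 days with *r* = 0.5, the ratio is (1 + 729 × 0.5)/(3.6 + 726.4 × 0.5) = 365.5/366.8, which is above 0.99. Any effect therefore sits in the early period and fades if events are spread over years.

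**Step 3: is the direction fixed?** Drop the assumption of equal reporting. With 50% reporting after myomectomy over 14 days, the captures are equal when 1 + 13*r* = 8.8, so *r* = 7.8/13 = 0.60 after UAE. Over 42 days they are equal when 1 + 41*r* = 22.8, so *r* = 21.8/41 = 0.53. Reporting after UAE above these values would reverse the bias. An open trial can produce a difference of that order in either direction.

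**The case against.** A reader might infer that adverse-event collection ends at discharge, giving the arms windows of 1 and 3.6 days and a safety comparison that favours UAE. The documents do not support that. The Treatment section sets no end at discharge, and the Secondary outcomes section continues collection throughout the study in both arms. The two stays are background figures in an argument about cost. Myomectomy here may be laparoscopic, hysteroscopic or by laparotomy, so 3.6 days need not be the trial's mean. Step 3 shows that the direction is open.

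Three further objections deserve weight.

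- **The Follow-up questions would reveal many events.** This stands in part. Readmissions and consultations with their reasons are asked about in both arms. But the article does not say that the answers become adverse-event reports, and an event managed at home without any contact would not appear. The schedule is also unclear: Follow-up says each time-point, while Table 1 marks clinical resource use only before randomisation, before discharge and at 6 months.
- **The article condenses a full protocol, and Figure 2 is not shown.** This also stands in part, since follow-up forms may contain adverse-event prompts. However, Table 1 does not leave the method out: for serious events it prints unsolicited reporting as the method.
- **The size is constructed.** This stands. Only the stays come from the document, and the ratios illustrate a mechanism; they do not estimate a bias.

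**Conclusion.** The point holds as one of ascertainment. After the procedure record, the article shows no scheduled adverse-event enquiry, and its stated route is unsolicited reporting. In an open trial with different expected stays, that gives unequal intensity of observation in the early post-procedure period, and the adverse-event comparison can be biased.

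Under-counting after UAE is plausible if reporting after discharge is incomplete and equal between arms. On that basis, with even timing of events, full in-hospital capture, the background stays and 30% to 80% reporting, the illustrative spurious risk ratio is 0.73 to 0.96 over 14 days and 0.88 to 0.98 over 6 weeks. Direction and size are not established. The primary quality-of-life outcome is not affected. The change is worth making because adverse events are a named secondary outcome and the remedy is cheap.

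**What to change.** 1. Add an adverse-event row to Table 1, covering serious and non-serious events. Use the same standard questions in both arms at the existing 6-week contact (already scheduled for the AMH sample) and on the existing 6-month, 1-, 2- and 4-year forms. Ask for onset dates.
2. Compare adverse events between arms over a fixed period from the procedure to 6 weeks, irrespective of discharge date. The fixed period alone is not enough: the 42-day table shows that passive capture can still distort it, so it must go with step 1.
3. Review readmissions and unplanned visits reported under Follow-up as possible adverse events, and reconcile the timing of those questions between Follow-up and Table 1.

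If the full protocol or Figure 2 already contains such questions, stating this in Table 1 is enough for step 1.

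The cost is a few questions at contacts and on forms that already exist. The small downside is more minor events to process.

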### Follow-up

The time-points when the various outcomes are recorded are shown in Table 1. At each time-point, details of any pregnancy will be collected alongside information on any resource use including:The number and reason of any additional out-patient visits and/or primary care consultations;Any additional procedures and inpatient stays;The type and dose of any medications received;Any further tests and interventions received;The information collected at each time-point is summarised in Figure 2, the study schema.

**Figure 2 Fig2:**
[figure not shown]
**FEMME study schema.** HMB, heavy menstrual bleeding; MRI, magnetic resonance imaging; PBAC, Pictorial Blood Loss Assessment Chart; UAE, uterine artery embolisation; UFS-QoL, Uterine Fibroid Symptom Quality-of-Life questionnaire.

### Outcome measures

The primary outcome for the FEMME study is the health-related quality of life (HRQL) score from the UFS-QoL questionnaire recorded two years post-procedure.

#### Primary and interim analysis

HRQL scores from the UFS-QoL will be analysed using a linear model (analysis of covariance) with estimates of difference between groups adjusting for the baseline score. Results of the primary outcome score at other time-points, along with the results of other continuous-type measurements (for example, symptom severity score from the UFS-QoL questionnaire, EQ-5D and Blood Loss scores) will be analysed in a similar fashion. Further analysis of continuous measures will be undertaken using a repeated measure multilevel model to examine any differential effect over time [12].

Dichotomous measures (for example, pregnancy or re-intervention rates) will be analysed using relative risks and chi-squared tests at each time-point. Variables, including pregnancy and any re-intervention, will also be explored using standard time-to-event analysis methods (log-rank test). All analyses will be performed using the intention-to-treat principle, with effect sizes presented as point estimates and corresponding 95% confidence intervals. A more comprehensive analysis plan will be made available for review by the Data Monitoring Committee (DMC).

An interim report, including the analysis of major endpoints, will be provided in strict confidence to the Data Monitoring and Ethics Committee at intervals of at least 12 months, or as requested by the DMC.

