## Background

### Why is there a need to determine whether treatment with uterine artery embolisation or myomectomy is most efficacious in improving the quality of life of women with uterine fibroids?

Uterine fibroids are the most common tumour in women of reproductive age and increase in prevalence as the woman gets older. By the time they are 50-years-old, around 80% of women will have developed a fibroid. Approximately half of women with fibroids experience significant symptoms which can include heavy menstrual bleeding (HMB), pain on intercourse, abdominal pain, and a feeling of pressure, all of which can impact significantly on the woman’s quality of life [1].

The symptoms experienced by the woman with fibroids may vary depending on the position, size and number of fibroids. Intramural fibroids are the most common form of fibroid but are frequently asymptomatic. Subserosal fibroids, located on the outer surface of the uterus, can become very large and create feelings of bulkiness. Submucosal fibroids project into the uterine cavity and are associated with HMB. As they may distort the uterus and change the local morphology of the uterine tissue, some clinicians believe that the presence of fibroids may have a negative impact on fertility [2]. The Hospital Episode Statistics state that there were just under 31,000 Finished Consultant Episodes of women with fibroids of the uterus between 2012 and 2013 in the United Kingdom. The majority of these women were aged between 40 and 54-years-old [3].

Women with symptomatic fibroids often respond poorly to drug management or risk unacceptable side effects from hormonal preparations [4], so generally the use of these pharmaceuticals is limited to reducing the fibroid bulk and relieving the symptoms prior to surgical intervention. The traditional treatment for symptomatic fibroids is hysterectomy, but with many women associating their uterus with their femininity and sexuality, an increasing number of women with fibroids are questioning whether hysterectomy for a benign condition is necessary and many are seeking alternatives.

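### The primary ANCOVA names only the baseline score and leaves out the three minimisation factors, so it may be slightly conservative; adding them is a free, low-severity improvement

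*Protocol article*

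**What the plan says.** Under Randomisation, the protocol article states: "A minimisation algorithm will be used to ensure that the groups are balanced as evenly as possible". Besides treatment group, the balancing variables are the longest dimension of the largest fibroid (two levels, split at 7 cm), the number of fibroids (three bands) and whether the woman wants to become pregnant (two levels).

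Under Outcome measures, the primary outcome is the "health-related quality of life (HRQL) score from the UFS-QoL questionnaire recorded two years post-procedure". Under Primary and interim analysis, this score is analysed by a linear model (ANCOVA) "with estimates of difference between groups adjusting for the baseline score". The same section applies the same approach to HRQL at other time-points and to the other continuous measures (symptom severity, EQ-5D, blood loss).

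The minimisation variables come back only under Subgroup analysis, as the sole candidates for interaction tests. No section puts them into the primary model.

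**The concern.** Minimisation removes most of the chance imbalance between arms on the three factors, so their variation contributes little to the difference between arms. A model without them still counts that variation as residual noise. If the factors are prognostic, the model's standard error is then larger than the real sampling error of the treatment estimate. The nominal 95% interval covers more than 95% of the time, the nominal 5% test rejects less than 5% of the time under the null, and some power that the design has already secured goes unused.

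What is at stake is efficiency and the accuracy of the stated coverage. The validity of the comparison is not at stake.

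**Working it through.** **Inputs from Sample size.** Effect 0.5 SD, 90% power, P = 0.05 (taken as two-sided), 86 per group, 172 in total, inflated to 216. The SD of 22 points comes from an ANCOVA, so it is taken as the residual SD after baseline adjustment and set to 1.

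**Reproducing the plan's figure.** For 0.5 SD at 90% power and two-sided 5%, the normal approximation gives 85 per arm and the noncentral t gives 86 (power 90.3%). By the normal approximation, 86 per arm has 90.6% power. Inflation: 172/0.80 = 215, against 216 stated. The plan's figures stand.

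**Assumed input.** R² is the share of the post-baseline residual variance explained by the three factors. The documents give no value, so 0 to 0.20 is shown.

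**Formulas** (n = 86 per arm, balance on the factors treated as complete):

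- SE reported by the baseline-only model: √(2/86) = 0.1525.
- True SE: √(1 − R²) × 0.1525.
- SE ratio: 1/√(1 − R²).
- Actual alpha, baseline-only: 2 × [1 − Φ(c)], where c = 1.96/√(1 − R²).
- Power, baseline-only: Φ(0.5/true SE − c).
- Power, adjusted: Φ(0.5/true SE − 1.96).

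For R² = 0.10: true SE = 0.9487 × 0.1525 = 0.1447; c = 1.96 × 1.054 = 2.066; 0.5/0.1447 = 3.456. Power is Φ(1.390) = 91.8% baseline-only and Φ(1.496) = 93.3% adjusted.

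| R² (assumed) | Reported SE too large by | Actual alpha | Power, baseline only | Power, adjusted | Gain (points) |
|---|---|---|---|---|---|
| 0 | 0% | 0.050 | 90.6% | 90.6% | 0 |
| 0.02 | 1.0% | 0.048 | 90.9% | 91.2% | 0.3 |
| 0.05 | 2.6% | 0.044 | 91.2% | 92.0% | 0.8 |
| 0.10 | 5.4% | 0.039 | 91.8% | 93.3% | 1.5 |
| 0.20 | 11.8% | 0.028 | 93.0% | 95.6% | 2.6 |

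**Simulation check.** 3,000 trials of 172 women, minimised on 2 × 3 × 2 factors, with an assumed 80% chance of the balancing allocation. The Monte Carlo standard error of alpha is √(0.05 × 0.95/3000) ≈ 0.004.

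- R² = 0.20: the baseline-only model reports SE 0.153 against an empirical 0.135, alpha 0.028, power 93.5%. The adjusted model reports 0.137 against 0.134, alpha 0.043, power 96.1%.
- R² = 0.10: baseline-only 0.153 against 0.147, alpha 0.044, power 91.1%. Adjusted 0.145 against 0.145, alpha 0.053, power 92.6%.
- R² = 0.05: the simulation is too small to show the effect. Empirical SEs were 0.154 for both models, alpha was 0.054 and 0.060, and power was 90.1% and 90.6%.
- R² = 0: the two models cannot be told apart.

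The simulation supports the formulas at R² of 0.10 and above and says little at 0.05.

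**The case against.** **The full analysis plan may already include the factors.** The article does not say that baseline is the only covariate, and it promises a more comprehensive plan. Under Economic evaluation it also refers to adjusting for relevant covariates in line with the clinical analysis, which could imply more than one. This is fair, and nobody should infer that the final analysis certainly omits them. But the article does state a covariate set for the primary model, so the point concerns what is written and is not a complaint about missing detail.

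**The effect is conditional.** A reader might infer that the standard errors are too large as a matter of fact. The documents do not support that. The Background says: "The symptoms experienced by the woman with fibroids may vary depending on the position, size and number of fibroids". That concerns symptoms in untreated women, which the baseline score may already capture, and it does not address HRQL two years after treatment. No passage links desire for pregnancy to HRQL. With R² near zero nothing is lost. This objection stands and is why the sizes are given as a range.

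**The gain is easily overstated.** It is tempting to set adjusted power against the planned 90%. That is not like for like, because the baseline-only analysis also benefits from the balance. The proper comparator is the baseline-only power in the table, which leaves 0.8 to 1.5 points at R² of 0.05 to 0.10.

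**Extension to binary outcomes.** A reader might carry the argument over to the relative risks and chi-squared tests for pregnancy and re-intervention. The article expects pregnancy in 10% or less before two years, at most about 22 of 216 women (0.10 × 216 = 21.6), and four extra terms with so few events could be unstable. No passage ties re-intervention to fibroid size or number. That extension is not made here. Covariates for the repeated-measures and imputation models are ordinary analysis-plan content and are not a fault of this article.

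**Conclusion.** The point holds in a limited form. The stated primary model does not reflect the minimised allocation, and the model for the other continuous outcomes follows it. If the factors carry prognostic information beyond the baseline score, the analysis is conservative. Over assumed R² of 0.05 to 0.20, the standard error is 2.6% to 11.8% too large, the nominal 5% test runs at 4.4% to 2.8%, and 0.8 to 2.6 points of power are forgone. At R² = 0 there is no effect.

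A reader might infer a biased estimate, an inflated type I error or an inadequate sample size. None of these follows: omitting balanced factors errs on the conservative side, and at 86 evaluable women per arm power stays at or above 90% throughout the range. The sizes rest on an assumed R², near-complete balance on the factors and a two-sided test. This is a free improvement of low severity.

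**What to change.** Under Primary and interim analysis, state that HRQL at two years will be analysed by ANCOVA adjusting for the baseline score and the three minimisation variables (largest-fibroid size, number of fibroids, desire for pregnancy), and that the other continuous outcomes handled in the same way will use their own baseline score plus these three variables. If the full analysis plan already says this, bring the published wording into line with it.

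The cost is one sentence and 4 degrees of freedom (1 + 2 + 1), which is negligible with 172 evaluable women. No new data are needed, because allocation requires all three variables for every woman. The change should be fixed before outcome data by arm are examined, so that there is no later choice between adjusted and less adjusted results. The sample size need not change.
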